### Intervention description {11a}

Participants randomized to the experimental arm and the active control arm will begin the intervention (CFT or ESS) within 1 month, to allow for the formation of a group of 8 individuals for each active arm.

Both therapies (CFT and ESS) will follow the same modality: groups of 8 participants, 12 sessions of therapy facilitated by 2 co-therapists (one senior psychologist and one mental health professional or peer support worker). The duration of each session will be 2 h including a 15-min break. For both therapies, a whiteboard and therapy manuals (booklets for the participants with summaries of key information and worksheets and booklets for the facilitators) will be provided with aims and contents for each session and examples of verbatim for the therapist. Both therapies will include in-between session practices for the participants.

Participants randomized to the TAU arm will pursue their routine care (including visits to their psychiatrist and other treatment modalities delivered in their routine care with the exception of specific psychotherapies, such as CBT).

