### Experimental or control therapies (12 weeks)

Participants randomized to the experimental arm and the active control arm will begin the intervention (CFT or ESS) within 1 month, to allow for the formation of a group of 8 individuals for each active arm. Participants randomized to the TAU arm will pursue their routine care.

Both therapies (CFT and ESS) will follow the same modalities: groups of 8 patients, facilitated by 2 co-therapists (one senior psychologist and one mental health professional or peer support worker). Sessions will have a duration of 2 h including a 15-min break, therapy manuals and a whiteboard will be used and both therapies will include homework practices.

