### Sample size {14}

Taking the effects obtained in the article *Effects of a group psychoeducation program on self-stigma, empowerment and perceived discrimination of persons with schizophrenia* [72], for the TAU and ESS groups and adding a CFT group with a stronger and lasting effect, the means and standard deviations of the ISMI before the therapy, after the therapy, and after 6 months follow-up used to estimate the sample size are respectively 2.46 ± 0.39, 2.43 ± 0.29, and 2.46 ± 0.39 for the TAU group; 2.45 ± 0.48, 2.20 ± 0.41, and 2.40 ± 0.48 for the psychoeducation group; and 2.45 ± 0.48, 2.10 ± 0.41, and 2.20 ± 0.48 for the CFT group. With 84 patients in each group, the power is more than 85% between the TAU and psychoeducation groups after the therapy and more than 99% between CFT and the other groups after 6 months. In order to consider the possible loss to follow-up, the sample size is increased by 33% to obtain 112 patients in each group. The total sample size is therefore 336 participants.

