### Recruitment {15}

A large network of professionals in institutions or in private practice (e.g., psychiatrists, psychologists) of the geographical area of all the participating centers of the study will be deployed to refer patients to the investigating teams. All the hospital centers are central coordinators of the care of patients with SMI and ASD in their respective areas; moreover, all of them propose care within a recovery model of psychiatric disorders. These factors guarantee that many patients with SMI and ASD can be recruited in these centers and that all centers will show high levels of implication in the recruitment and adherence to the psychotherapeutic models proposed.

Patients will be recruited into the psychiatric and mental health department of each center during a routine clinical consultation. The inclusion period is 48 months. This is a realistic duration given the significant number of patients to be enrolled. The study is scheduled to involve 7 French national centers, with 24 patients to be enrolled per center (one randomization blocks of 24 patients—3 groups of 8 patients in CFT, ESS, and TAU—in each center; the Strasbourg center will recruit 192 patients, i.e., 8 randomization blocks).

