### Assignment of interventions: allocation

#### Sequence generation {16a}

Randomization will be done through the CleanWEB® platform, which will be accessed by the investigator or a designated person, using their personal access codes. The investigating team and the sponsor will receive an email confirming the randomization. Patients will be randomized over a period of 1 month before the start of the interventions, to allow the 3 groups of treatment to be formed (CFT, ESS, TAU), so that each group starts the allocated therapy at the same time.

The randomization will be stratified by center, with a 1:1 ratio for allocation to the 3 groups. Patients will be recruited until they form a group of 24 people allowing to randomize them in one of the 3 conditions, in groups of 8 people matched on gender and diagnostic group (4 possibilities: (1) psychotic disorder, (2) mood disorder, (3) personality disorder, and (4) autism spectrum disorder, referring to (1) schizophrenia-spectrum disorder, (2) bipolar disorder and depression, (3) borderline personality disorder, and (4) autism spectrum disorder). This process will be reiterated at least once in each center:

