## Statistical methods

### Statistical methods for primary and secondary outcomes {20a}

The statistical analysis will have descriptive and inferential. The analyses will be carried out according to Bayesian methods.

The descriptive statistical analysis of the categorical variables will be performed by giving the frequencies, the cumulative frequencies, the proportions, and the cumulative proportions of each value. Whenever useful, cross-tabulations will be given with frequencies, proportions by row, proportions by column, and proportions of the total for each box in the table. For each continuous variable, the location parameters (mean, median, minimum, maximum, first and third quartiles) and the dispersion parameters (variance, standard deviation, range, interquartile range) will be given. The continuous variables will be described with histograms (with different bin width and with kernel density estimation). The normality of the distributions will be tested using a normality test, such as the Shapiro-Wilk test, and will be assessed graphically using a normal quantile plot.

To fulfill the primary objective, a generalized Bayesian linear regression model will be performed in order to estimate the effect of the treatment considering the center and the subject as a random effect. According to the distribution of the primary endpoint, i.e., the ISMI, the linear regression will be Gaussian, beta, or gamma.

To fulfill the secondary objectives, a generalized Bayesian linear regressions model will be performed: binary variables will be analyzed with a Bayesian logistic regression, score variables will be analyzed with a Bayesian beta regression, count variables will be analyzed with a Bayesian Poisson regression, and continuous variables will be analyzed with a Bayesian linear regression.

Priors will be firstly weakly informative and secondly more informative in a sensitivity analysis.

For each analysis, the posterior distribution of the parameter of interest (rate, proportion, mean, odds-ratio, regression coefficient, etc.) will be estimated using Markov chain Monte Carlo (MCMC) draws. The default number of iterations is 100,000 with a burn-in of 10,000 and a thinning of 2 on each of 3 chains. Algorithm convergence will be assessed graphically and with the Gelman-Brooks-Rubin (GBR) test. Autocorrelation will be assessed graphically, and if required, the number of iterations and thinning will be increased to reduce as much as possible the autocorrelation.

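### CFT and ESS are delivered in pre-formed groups of 8, but the primary model has random effects for centre and subject only, so CFT contrasts may be declared too often if outcomes cluster by therapy group.

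*Protocol article*

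**What the plan says.** Delivery is by group. Section {11a} sets out "groups of 8 participants, 12 sessions of therapy facilitated by 2 co-therapists" for both CFT and ESS. Participants start within a month of randomization, "to allow for the formation of a group of 8 individuals for each active arm". Section {16a} has patients randomized over a month before the start, "so that each group starts the allocated therapy at the same time". The TAU arm has no therapy group: "Participants randomized to the TAU arm will pursue their routine care".

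The layout is in Recruitment {15}: six centres contribute one block of 24 patients each, and "the Strasbourg center will recruit 192 patients, i.e., 8 randomization blocks". Each block yields one CFT group, one ESS group and one TAU set of 8.

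The primary model in {20a} is a Bayesian regression for the treatment effect, "considering the center and the subject as a random effect". An effect is declared when its posterior probability lies above 0.975 or below 0.025. No therapy-group or therapist term appears there or in {20b} or {20c}.

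Sample size {14} uses patient-level means and SDs, and its only inflation is for loss to follow-up. It states: "With 84 patients in each group, the power is more than 85% between the TAU and psychoeducation groups", and above 99% for CFT against the other arms at 6 months.

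**The concern.** Patients who spend 12 sessions together under the same two facilitators are likely to end up more alike than patients drawn at random from the arm. The protocol itself treats group process as relevant: it measures group cohesion at sessions 1, 6 and 12, and its Discussion lists varying facilitator backgrounds as a limitation.

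The two named random effects do not cover this.

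- **Centre.** One intercept is shared by all three arms, so it drops out of within-centre contrasts. A group effect belongs to one arm and stays in the contrast. In the coordinating centre, which holds 192/336 = 57% of patients, one intercept spans 8 CFT groups and 8 ESS groups.
- **Subject.** This effect ties together repeated measures on one person. Given centre, it treats members of one group as independent.

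At stake is the error rate of the primary comparison. CFT versus ESS is part of the primary objective and is the contrast most exposed, because both of its arms are clustered.

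**Working it through.** **Inputs.** Groups: (6 × 24 + 192)/24 = 336/24 = 14 blocks, so 14 CFT and 14 ESS groups (112/8 = 14). Members per group, m: 8 as randomized, or 84/14 = 6 with the evaluable number in {14}. ICC: not given, so 0.01 to 0.10 is assumed. The decision rule behaves roughly like a two-sided 5% test under weak priors.

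**The plan's own figure.** TAU versus ESS after therapy: difference 2.43 − 2.20 = 0.23; SE = √((0.29² + 0.41²)/84) = 0.0548; power = Φ(0.23/0.0548 − 1.96) = 98.7%. The statement of at least 85% therefore holds without clustering. With a design effect DE applied to the ESS arm only, SE = √((0.29² + DE × 0.41²)/84):

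- DE 1.25: SE 0.0592, power 97.3%
- DE 1.50: SE 0.0633, power 95.3%
- DE 1.70: SE 0.0664, power 93.4% (this pairs the 8-per-group design effect with 84 patients, so it is harsher than either consistent scenario)

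It still holds.

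**Error rate when the group is ignored.** DE = 1 + (m − 1) × ICC. The true variance of CFT minus ESS exceeds the modelled variance by a factor DE. For CFT minus TAU, with equal variances and only one arm clustered, the factor is (DE + 1)/2. Actual error = 2 × (1 − Φ(1.96/√factor)).

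| m | ICC | DE | CFT–ESS | CFT–TAU |
|---|---|---|---|---|
| 6 | 0.01 | 1.05 | 5.6% | 5.3% |
| 6 | 0.02 | 1.10 | 6.2% | 5.6% |
| 6 | 0.05 | 1.25 | 8.0% | 6.5% |
| 6 | 0.10 | 1.50 | 11.0% | 8.0% |
| 8 | 0.01 | 1.07 | 5.8% | 5.4% |
| 8 | 0.02 | 1.14 | 6.6% | 5.8% |
| 8 | 0.05 | 1.35 | 9.2% | 7.1% |
| 8 | 0.10 | 1.70 | 13.3% | 9.2% |

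**Check by simulation.** A frequentist simulation used the trial's layout: 14 blocks in 7 centres, 25% loss, baseline correlation 0.6, centre adjusted, no group term, 4,000 runs. For CFT–ESS it gave 4.8% at ICC 0, 6.0% at 0.02, 8.2% at 0.05 and 11.5% at 0.10. For CFT–TAU it gave 4.8%, 5.3%, 5.3% and 7.9%. The 5.3% at ICC 0.05 lies below the formula's 6.5%; a 20,000-run repeat of the same layout gave 6.7%. The centre term does not remove the inflation.

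**Power for the CFT contrasts, 84 per arm, m = 6.** For CFT–ESS, effective n = 84/DE, that is 80, 67 and 56 at ICC 0.01, 0.05 and 0.10.

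- V1, difference 0.10, SD 0.41: 35% without clustering, then 34%, 29% and 25%.
- 6 months, difference 0.20, SD 0.48: 77% without clustering, then 75%, 68% and 60%.
- CFT–TAU at 6 months, difference 0.26, SE = √((DE × 0.48² + 0.39²)/84): 97% without clustering, then 97%, 95% and 92%.

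**Where the group term has to act.** Participants have not met as a group at V0, so the group effect arises afterwards. The subject effect implies repeated measures, and {12} defines success by the V0-to-V1 decrease. A group intercept held constant over visits subtracts out of that change. Take ICC 0.10 at V1 only, unit variances, correlation 0.6 and m = 6. The change has variance 2 × (1 − 0.6) = 0.8, its group share is 0.10/0.8 = 0.125, DE = 1 + 5 × 0.125 = 1.625, and the error is 2 × (1 − Φ(1.96/√1.625)) = 12.4%. A simulation with subject and visit-constant group intercepts gave 12.8% (343 mixed-model fits), essentially uncorrected. Analysing group-mean changes restored about 5%.

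**The case against.** The strongest objection is that the size rests wholly on an ICC that the protocol does not give. At ICC 0 there is no inflation, and at 0.01 it is under one percentage point. This stands: the effect is conditional, and a reader who infers that CFT effects certainly will be over-declared goes further than the document allows.

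Four other stronger readings are tempting and also unsupported.

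- **Clustering breaks the stated power.** The TAU–ESS figure survives every scenario above. The figure above 99% at 6 months already fails without clustering (77% for CFT–ESS, 97% for CFT–TAU at 84 per arm). That is a separate sample-size matter.
- **Every group has its own facilitators.** The protocol says two co-therapists per group. It does not say they differ between groups, and one pair could lead several groups in the coordinating centre.
- **The secondary models are also wrongly fixed.** Section {20a} names random effects for the primary model only.
- **The group identifier is already in the data.** No section says that it is recorded.

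It could also be said that random-effects detail belongs in an analysis plan. That would hold if the article were silent. It instead names the random effects of the primary model and leaves out the level at which treatment is delivered, so a plan that follows it carries the gap forward.

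**Conclusion.** The point holds in conditional form. The protocol sets up 14 therapy groups in each active arm, and the primary model as written cannot represent variation between them. Whenever the therapy-group ICC is positive, the posterior SDs for the CFT contrasts are understated. For an assumed ICC of 0.01 to 0.10 and 6 to 8 members assessed, a nominal 5% error becomes about 5.6% to 13% for CFT–ESS and 5.3% to 9% for CFT–TAU. With the 6 per group implied by 84 evaluable patients, the upper ends are 11% and 8%. These figures assume weak priors, and for CFT–TAU equal variances in the two arms. The consequence ranges from negligible to a more than doubled error rate on CFT–ESS. It bears on the primary inference and is cheap to remove, so it should be settled before analysis.

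**What to change.** In {20a}, add to the primary model a partially nested therapy-group random effect: present in the CFT and ESS arms, absent for TAU. It must act on post-baseline outcomes. Two forms do this: a group-by-visit effect fixed at zero at V0, or a group intercept in a model of V1 adjusted for V0. A group intercept constant over visits does not do the job. Give the group SD a weakly informative prior, report the posterior ICC, and use the same structure in the secondary models.

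In {14}, state that the power figures assume independent patients, and give power for CFT versus ESS and CFT versus TAU with a design effect of 1 + (m − 1) × ICC in the active arms, over a stated ICC range.

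The cost is one model term, a few sentences, slightly wider credible intervals, a less favourable power statement for the CFT contrasts, and making sure that each participant's therapy group is recorded in the database. If the same facilitators lead several groups, recording them too would show whether clustering extends beyond the group.

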Among the interventions designed to reduce self-stigma in people with SMI, group psychoeducation has been the most studied [26–28]. In particular, the Ending Self-Stigma (ESS) program [12, 29, 30] is among the rare interventions whose efficacy has been tested via a randomized controlled trial (RCT) [30]. The ESS program is a 9-session manualized group intervention during which participants learn skills aimed at reducing self-stigma. Sessions consist of learning cognitive strategies (e.g., identifying and changing self-stigmatizing thoughts) and problem solving. In their study, Lucksted et al. [30] compared this intervention to treatment as usual (TAU) and found an immediate improvement in the alienation and stigma resistance subscales of the Internalized Stigma of Mental Illness Scale (ISMI) [31] but no improvement on the total self-stigma score. Moreover, the effects were modest, failed to be significant at 6 months of post-treatment follow-up, and the authors reported a very high drop-out rate and low attendance (only 43% of participants attended at least 7 sessions). Similar results suggesting the high attrition rate of the ESS have been reported in a more recent study [12]. The latter indicates no superior effects of ESS compared to a nonspecific health and well-being program. These different trials emphasize the limitations of the ESS (e.g., the attrition rates, the inconclusive results when the ESS was compared to an active control group, and the lack of sustainability of self-stigma outcomes at follow-up). Given that the affective component of self-stigma, i.e., shame, was not targeted by the ESS, we hypothesize that high levels of shame lingered post-therapy leading both to social avoidance and high rates of drop-out.

Overall, despite the aforementioned limitations, psychoeducation programs such as the ESS [30] remain recommended in recent meta-analyses and systematic reviews as they cumulated the highest level of evidence for reducing self-stigma associated with SMI. The aim of our compassion-focused intervention is to address the main limitations of more traditional approaches that do not address the shame associated with self-stigma. To do so, unlike traditional CBT and psychoeducation programs, our intervention aims to directly target the affective component of self-stigma, i.e., shame [13, 17], through compassion-focused therapy (CFT) [16, 32].

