#### Objectives {7}

The primary objective of our study is to evaluate the efficacy of a 12-week CFT group in decreasing self-stigma associated with severe psychiatric disorders and ASD by comparing its immediate effects to the effects of the Ending Self-Stigma (ESS) psychoeducation program [29] and to TAU.

The secondary objectives of our study are as follows:1. To evaluate the maintenance of effects on self-stigma scores in the three groups of treatment (CFT, ESS, and TAU) at 6-month follow-up (V2)2. To assess the effects of treatment (CFT, ESS, and TAU) at baseline (V0), post-treatment (V1), and at 6 months follow-up (V2) on target psychological dimensions (shame, self-compassion, emotional regulation, automatic avoidance tendencies toward mental illness)3. To assess the effects of treatment (CFT, ESS, and TAU) at baseline (V0), post-treatment (V1), and at 6 months follow-up (V2), on social functioning and psychiatric measures (psychiatric symptoms, depression, anxiety and stress, social functioning, access to care, recovery, functional remission)4. To assess the psychological factors mediating (shame, self-compassion, and emotional dysregulation) the efficacy of CFT on the self-stigma measure (V1)5. To evaluate the acceptability of the active interventions (CFT and ESS): pretreatment (V0) via a treatment credibility measure, during treatment via attrition rate, session attendance and group cohesion, and post-treatment (V1) via patient satisfaction and treatment side effects In addition, in the coordinating center, qualitative interviews will assess the acceptability of the active interventions.

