To evaluate the *acceptability* of the active interventions (CFT and ESS):• The Credibility and Expectations Questionnaire [68, 69] will be applied to assess self-reported treatment credibility at V0. This questionnaire contains 6 items rated either from 1 to 9 or from 0 to 100% and evaluates whether the participants “think” or “feel” that their treatment will be efficient.• The Group Questionnaire [70] will be used to measure group cohesion 3 times during the intervention (sessions 1, 6, and 12). It consists of 30 items addressing the group leaders, the other group members, and the group in general. Each item is scored using a scale ranging from 1 (not true at all) to 7 (very true).• The Consumer Satisfaction Questionnaire for Psychotherapeutic Services (CSQ-8) [71] will be applied as a self-report measure assessing participants’ satisfaction at the end of the 12-week program. The 8 items are scored on a scale ranging from 1 to 4. Higher scores are indicative of elevated satisfaction.• The attendance rate will be determined by the number of group sessions attended by the patient, and the drop-out rate will be determined by the number of patients lost to follow-up in each arm. In addition to the Consumer Satisfaction Questionnaire for Psychotherapeutic Services questionnaire (CSQ 8) [71], the avoidance of participants (due to self-stigma) in several social situations during the last 6 months, and the satisfaction with the interventions will be assessed via semi-structured interviews conducted at V2 by clinician-researchers blind to the status of patients (in the Strasbourg center only, for the 3 groups—CFT, ESS, and TAU).

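### By variable type, sessions attended (a total capped at 12) falls under the Poisson rule for counts, which ignores the cap, fixes variance equal to mean and will generally miscalibrate the CFT-ESS attendance interval

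*Protocol article*

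**What the plan says.** Secondary objective 5 (Objectives {7}) concerns the acceptability of the two active programmes, assessed partly "during treatment via attrition rate, session attendance and group cohesion". The outcome is defined under Secondary outcomes: "The attendance rate will be determined by the number of group sessions attended by the patient". Its ceiling comes from Intervention description {11a}, which gives both therapies the same format: "groups of 8 participants, 12 sessions of therapy facilitated by 2 co-therapists".

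Statistical methods {20a} then assigns a likelihood to each type of secondary variable. Two parts matter here: "binary variables will be analyzed with a Bayesian logistic regression" and "count variables will be analyzed with a Bayesian Poisson regression". Scores go to beta regression and continuous variables to linear regression. The rule has no entry for a number of successes out of a fixed total, and no dispersion term. The random effects ("considering the center and the subject as a random effect") are stated for the primary objective only. An effect counts as significant when its posterior probability is above 0.975 or below 0.025, and 95% credibility intervals are reported.

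The only attendance figure in the article comes from an earlier trial of the 9-session ESS programme, in Background and rationale {6a}: "only 43% of participants attended at least 7 sessions". The same paragraph describes very high drop-out in that trial.

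**The concern.** A per-patient session total is a count, so an analyst following {20a} as written is led to Poisson. Two features of the total do not fit that model. It cannot exceed 12, and its spread depends on how attendance is distributed over patients. A programme from which some patients quit early while others complete gives a wide spread. A programme that nearly everyone attends gives a very small one. Poisson allows neither, because it ties the variance to the mean.

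At stake is the attendance comparison between CFT and ESS. Poor attendance at ESS is one of the limitations that the background and discussion say CFT is meant to address, so readers will look at this contrast. An interval that is too narrow could lead to a declared difference that is not there. One that is too wide could hide a real gain in retention.

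**Working it through.** The plan states no figure that rests on the attendance model, so there is none to reproduce. The check compares the variance that Poisson assumes with the variance a total out of 12 would have.

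**Inputs from the article.** 12 sessions per active arm; 112 patients per arm (Sample size {14}); 95% intervals; 43% attending at least 7 sessions of a 9-session programme in the earlier ESS trial.

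**Assumptions.** Sessions attended follow a beta-binomial distribution with mean proportion p and within-patient session correlation ρ. The article does not give ρ, so a range is shown. For each ρ, p is solved so that P(at least 7 of 9) = 0.43, and that p and ρ are carried over to 12 sessions. There is no true difference between arms, and the priors are weak enough that the posterior follows the likelihood.

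**Formulas.** Mean = 12p. Variance = 12p(1−p)(1+11ρ). Poisson assumes variance = mean, so the ratio is

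R = variance/mean = (1−p)(1+11ρ).

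The true standard error of the log ratio is √R times the Poisson one. The actual error of a nominal 5% rule is 2[1−Φ(1.96/√R)]. The number of patients cancels. An offset for 12 sessions would be the same for everyone and would not change R.

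**Results, calibrated to 43%.**

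| ρ (assumed) | p | R = (1−p)(1+11ρ) | √R | actual error |
|---|---|---|---|---|
| 0.05 | 0.675 | 0.325 × 1.55 = 0.50 | 0.71 | 0.6% |
| 0.1 | 0.663 | 0.337 × 2.1 = 0.71 | 0.84 | 2% |
| 0.2 | 0.639 | 0.361 × 3.2 = 1.16 | 1.07 | 7% |
| 0.3 | 0.614 | 0.386 × 4.3 = 1.66 | 1.29 | 13% |
| 0.4 | 0.588 | 0.412 × 5.4 = 2.2 | 1.49 | 19% |
| 0.5 | 0.561 | 0.439 × 6.5 = 2.85 | 1.69 | 25% |

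**Good attendance.** With p = 0.85 to 0.90 and ρ = 0.1, R = 0.15 × 2.1 = 0.32 down to 0.10 × 2.1 = 0.21. The interval is then about 1.8 to 2.2 times too wide (1/√R), and the error is below 0.1%.

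**Where Poisson happens to be right.** R = 1 when ρ = p/[11(1−p)]: 0.14 at p = 0.6, 0.21 at p = 0.7, 0.36 at p = 0.8. The adequate band around 0.1 to 0.2 therefore belongs to the attendance level calibrated above and moves up as attendance improves.

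**Simulation check.** Over 5,000 trials of 112 versus 112 with a Poisson log rate ratio, coverage of the nominal 95% interval was 92% at p = 0.7, ρ = 0.3; 77% at p = 0.6, ρ = 0.5; and 100% at p = 0.8, ρ = 0. The formula gives 91.6%, 77.6% and 100%.

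**Drop-out modelled directly.** Suppose a constant chance h of quitting before each session, including the first, and attendance at 80% to 100% of sessions until then. With 100%, (1−h)^7 = 0.43 gives h = 0.114, and over 12 sessions R is about 3.3. With 80%, h is about 0.065 and R is about 2.2. The nominal 5% error becomes about 18% to 28%.

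**The ignored cap.** A Poisson model puts 3% of its probability above 12 sessions at a mean of 7.2, 8.5% at 8.4, 17% at 9.6 and 29% at 10.8.

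**The case against.** The strongest reply is that the article never says attendance will be fitted with Poisson. It lists families by variable type without mapping outcomes to them, and it calls the outcome a rate. An analyst could treat it as a bounded proportion or as session-level binary data, using the beta or logistic families already named. Other variables, such as side effects or adverse events, could be the counts the rule has in mind. The article condenses a longer protocol, and the likelihood for one component of the fifth secondary objective is often left to the analysis plan. This stands in part: Poisson for attendance is inferred. But the definition is a number of sessions and the rule for counts is explicit, so the natural reading leads to the wrong family. The point concerns that stated rule, and does not rest on missing detail.

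Second, the size rests on an assumed ρ and on one figure from a different 9-session trial. That figure cannot determine two parameters and may not carry over, because this trial adds two individual engagement sessions before the groups start. This stands. A reader might infer that the attendance interval is certain to be wrong, or wrong in the direction of false positives. The documents do not support either: the cap and the clustering pull in opposite directions and can nearly cancel.

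Third, a reader might infer that Poisson would treat a patient's sessions as independent rows. It would be fitted to one total per patient, so the fault is the variance assumption and the missing bound.

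Fourth, attendance sits beside credibility, cohesion, satisfaction and drop-out, with no hypothesis, threshold or confirmatory test of its own. A reader might take it for a key endpoint, but the article gives it no such standing.

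Finally, patients attend in groups of 8, and a beta-binomial model does not by itself allow for correlation within a group. That is correct, and it limits what the fix achieves.

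**Conclusion.** The point holds in a limited form. Followed as written, the type-based rule puts a total bounded at 12 into a model with no upper limit and variance equal to the mean. The resulting CFT-ESS interval will generally be miscalibrated. Under the early-quitting pattern that the article reports for ESS, it is too narrow: variance/mean of 1.7 to 2.9 and an actual error of about 13% to 25% for an assumed ρ of 0.3 to 0.5. Under uniformly good attendance it is too wide. At the cited attendance level it is roughly adequate for ρ between 0.1 and 0.2 (error 2% to 7%). These figures depend on the beta-binomial assumption, the assumed correlation and the transfer from 9 to 12 sessions. The consequence is confined to one secondary acceptability measure. The primary ISMI analysis and the sample size are not affected.

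**What to change.** Exempt attendance from the Poisson rule in {20a}. State that sessions attended out of 12 will be analysed with a Bayesian beta-binomial regression, or a binomial regression with a patient-level random effect, and that the CFT-ESS difference in attendance proportion will be reported with its 95% credibility interval. Poisson can stay for counts with no fixed maximum. A therapy-group term could be considered alongside, since the beta-binomial does not cover that source of correlation.

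The cost is one line of wording and one extra dispersion parameter. The model can be fitted in the JAGS or OpenBUGS software already named, and no data collection changes.
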